#### Quality control of radiographic examination

An abdominal and pelvic enhanced CT scan is important for clinical diagnosis and tumor staging. We ensure that the following items are determined with the CT scan: tumor location, tumor size, presence or absence of abdominal effusion, other abdominal organ metastasis, non-local LNM, and abnormal variation of peripheral gastric blood vessels; these aspects are included in the imaging report template.

#### Research supervision committee

We ensure that members of the research supervision committee of this trial have a clear division of labor and good cooperation. The supervision committee consists of data managers, data inspectors, and methodological teams. Each part of this clinical trial has a standard operating procedure to ensure the homogeneity of the research. Moreover, specialized personnel is engaged in data collection, data entry, data inspection, data cleaning, and follow-up.

### Statistical analysis

SPSS 21.0 (IBM Corp., Armonk, NY, USA) statistical software is used for the statistical analysis. The quantitative variables are described as the mean ± standard deviation and are tested by univariate analysis of variance for normal distribution; on the contrary, they are described as the median (interquartile range) and tested by the Kruskal-Wallis H test for non-normal distribution. The categorical variables are described as frequency (N) with the percentage (%) and tested by χ^2^ test, corrective χ^2^ test, or Fisher’s exact test. Ranked data are expressed as frequency and percentages and are compared using the Kruskal-Wallis H test. Sensitivity and specificity are calculated to evaluate the diagnostic performance. The Kaplan-Meier method is used to draw survival curves, and the survival of multiple groups are compared by the log-rank test. The univariate and multivariate Cox proportional hazards models are used to evaluate the hazard ratios for adverse outcomes. All statistical tests are two-sided, and a *P*-value < 0.05 is considered statistically significant.

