### Study design and setting

This is a multicenter, ambispective, observational, open-cohort study. The clinical trial was launched in May 2018 and will end in March 2022, with enrollment to be completed by December 2021. Between May 2018 and December 2022, patients from Beijing Friendship Hospital, Capital Medical University, Beijing Cancer Hospital, Peking University People’s Hospital, Peking University First Hospital, Chinese PLA General Hospital, and Cancer Hospital Chinese Academy of Medical Sciences will be selected for treatment. In total, 554 patients are expected to be included in the trial. After providing written informed consent, patients will undergo a D2 gastrectomy in a non-randomized, prospective study. For the retrospective study, researchers will recruit patients from January 2008 to April 2018, and all enrolled patients must meet the inclusion criteria. The detailed research process is described in Fig. 1. The latest protocol version is version 1.0 in April 2018.

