#### Follow-up

The postoperative follow-up is performed by a dedicated investigator. The patients are followed up every 6 months after discharge using outpatient visits, telephone, or mail. During the follow-up period, the patients undergo physical examinations, laboratory tests, a gastroscopy, a chest and abdominal CT scan, or an abdominal ultrasound assessment. The laboratory tests include routine blood examination, blood biochemistry, and tumor marker evaluation that includes CA19–9, CA125, AFP, CEA, and CA724. For patients that develop postoperative tumor recurrence or distant metastasis, a further detailed evaluation, including abdominal magnetic resonance imaging or PET/CT, will be performed to determine the feasibility of surgical resection. Each patient will be followed for at least 5 years or until a loss to follow-up. The detailed follow-up schedule is shown in Table 3.

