### Determination of sample size

The sample size was calculated by PASS 11.0 (NCSS Statistical and Data Analysis, USA) software and was estimated based on the preliminary research results of the Japanese clinical trial. According to previous studies with a single group design, the rate of LNM with expanded indications for ESD was 3% [20, 21] with an allowable error of 1.5%. Based on a one-sided test with an α value equal to 0.025, the estimated total sample size required for the trial is at least 497 patients. The withdrawal rate was assumed to be 20% during the follow-up. Therefore, the total sample size that is needed for this clinical study is approximately 554 patients, of which 274 and 280 are enrolled in a prospective- and retrospective study, respectively.

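### The relapse-free survival methods name no handling of cohort, although 280 of the 554 patients were operated on before launch and most of their relapse follow-up must come from existing records

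*Protocol article*

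**What the plan says.** The Statistical analysis section sets out the survival methods: "The Kaplan-Meier method is used to draw survival curves, and the survival of multiple groups are compared by the log-rank test". It then names univariate and multivariate Cox models. It does not define the groups to be compared or list the Cox covariates, and it names cohort neither as a stratum nor as a covariate, nor as a reason for separate analyses.

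The sample is made of two parts, "of which 274 and 280 are enrolled in a prospective- and retrospective study, respectively" (Determination of sample size). For the retrospective part, "researchers will recruit patients from January 2008 to April 2018" (Study design and setting). The same section puts launch in May 2018, the end of enrolment in December 2021 and the end of the study in March 2022.

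The Follow-up section gives one schedule without distinguishing cohorts: "The patients are followed up every 6 months after discharge using outpatient visits, telephone, or mail". It promises each patient at least 5 years unless lost. Table 3 likewise gives one checklist for enrolled patients, with recovery outcomes at postoperative days 1, 3, 7 and 30, and abdominal CT every 6 months. Under Secondary endpoints, relapse-free survival is timed from operation to the detection of recurrence, and complications are counted over 30 days.

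**The concern.** An endpoint that ends at detection depends on how and when relapse is looked for. A schedule introduced in 2018 cannot have governed the care of a patient operated on in 2010, so the two cohorts differ in ascertainment for much of the follow-up. If relapse was recorded less completely or later before launch, an unstratified analysis has two weaknesses. A combined 5-year rate could look better than it is. And if the retrospective share differs between indication categories, a log-rank or Cox comparison of those categories would partly reflect the source of the data. The 30-day complication rate would mix prospectively collected outcomes with outcomes abstracted from records.

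The primary endpoint, lymph node metastasis, is read once from the surgical specimen and is not affected by this point.

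**Working it through.** **Inputs from the protocol article.** 274 prospective and 280 retrospective patients (274 + 280 = 554); retrospective window January 2008 to April 2018 (124 months); prospective enrolment May 2018 to December 2021; stated end March 2022. The only sample-size calculation concerns the lymph node metastasis rate: 1.96² × 0.03 × 0.97 / 0.015² = 496.8, which reproduces the stated 497. No event count or precision is given for relapse-free survival, so there is no plan figure to reproduce for this endpoint.

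**Assumptions of this check.** Uniform accrual within each window, administrative censoring only, and 31 March 2022 as the data cut where one is used.

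**Step 1: share of retrospective follow-up before launch.** Operations from January 2008 to April 2013 (64 months) have their whole 5-year window before May 2018. Operations from May 2013 to April 2018 (60 months) have on average half of it before launch.

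(64 × 1 + 60 × 0.5) / 124 = 94 / 124 = 75.8%.

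The whole window precedes launch for about 280 × 64 / 124 = 145 patients. The other 135 or so can have some follow-up after launch. For 30-day outcomes, only operations in the last weeks of the window could reach day 30 after launch; 280 / 554 = 50.5% of the sample is in this cohort.

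**Step 2: risk set at a March 2022 cut.** Possible follow-up runs from 2.96 to 46.98 months in the prospective cohort and from 47.01 to 170.94 months in the retrospective cohort. The number still under observation at month t is

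- prospective: 274 × (46.98 − t) / 44.02, for t from 2.96 to 46.98
- retrospective: 280 up to month 47.01, then 280 × (170.94 − t) / 123.93

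| Month | Prospective | Retrospective | Prospective share |
|---|---|---|---|
| 0 | 274 | 280 | 49.5% |
| 12 | 217.7 | 280 | 43.7% |
| 24 | 143.0 | 280 | 33.8% |
| 36 | 68.3 | 280 | 19.6% |
| 42 | 31.0 | 280 | 10.0% |
| 48 | 0 | 277.8 | 0% |
| 60 | 0 | 250.7 | 0% |

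**Step 3: risk set if every patient is followed for 5 years.** The last prospective patient would reach 5 years in December 2026. The prospective share then stays near 274 / 554 = 49.5% through month 60. The changing mix is gone; the 75.8% in Step 1 is unchanged.

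**Step 4: illustration only.** Nothing in the documents says what fraction of relapses pre-launch follow-up recorded. Take a constant hazard, a true 5-year relapse-free rate of 90% in both cohorts, and all patients in one curve. If pre-launch follow-up captured 80% or 60% of relapses, a March 2022 cut would give about 91% or 92%. With full 5-year follow-up it would give about 90.7% or 91.5%. With complete capture there is no distortion.

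**The case against.** The strongest objection is that the article does not state a pooled analysis. The survival sentence is a general methods line, the groups and covariates are left open, and the design section describes the prospective and retrospective studies separately. Strata and covariates for a secondary endpoint may well be set in a fuller document that is not shown. This stands: a reader might infer that the plan fixes one curve with no cohort term, but the text is only silent. What remains is that the stated methods, followed as written, permit an unstratified analysis.

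A reader might also infer that scheduled visits exist only in the prospective cohort. The documents do not say so. The Follow-up section and Table 3 apply one schedule to all enrolled patients, and operations from about May 2013 leave some follow-up after launch. The calendar supports only the narrower statement that follow-up before May 2018 was not done under this study. How the centres followed patients before then is not described.

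The drift to a retrospective-only risk set depends on taking March 2022 as the data cut, which conflicts with the 5-year minimum. That conflict is a separate matter. The drift also has no bearing on 30-day complications, which are a simple incidence; there, only the difference in ascertainment matters.

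Finally, the capture rates in the illustration are assumed, no figure shows that the retrospective share differs between indication categories, and stratifying cannot restore relapses missed within the retrospective stratum. All of this stands and limits what the fix can be said to achieve.

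**Conclusion.** The point holds in a limited form. The survival methods name no handling of cohort, in a study where just over half the patients had surgery before launch and the relapse endpoint depends on detection. Under uniform accrual and no losses, about 76% of the retrospective cohort's 5-year follow-up precedes launch. At a March 2022 cut, no prospective patient is observed beyond about month 47, against about 251 of 280 retrospective patients at month 60, so any single 5-year rate would rest on the retrospective cohort alone over its last 13 months. With 5 years for everyone this shift disappears and the ascertainment difference remains.

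The documents do not establish a bias of any particular size, or even that relapse was under-recorded before launch. This is an inexpensive improvement to a secondary analysis, not a demonstrated error.

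**What to change.** In the Statistical analysis section:

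1. Stratify the log-rank tests and Cox models for relapse-free survival by cohort (prospective or retrospective).
2. Show Kaplan-Meier curves by cohort, with numbers at risk, beside any pooled 5-year rate. Quote the prospective result only up to the follow-up actually reached.
3. Report 30-day complications by cohort. Naming the prospective cohort as the main estimate is optional.

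Cohort is known for every patient, so only the analysis wording changes. The costs are wider intervals for the cohort-specific estimates and, at a March 2022 cut, no prospective 5-year estimate at all. Stratifying keeps cohort from confounding the group comparisons, and the separate curves show the reader where the data come from. The report should say plainly that neither step corrects for relapses missing from, or dated late in, the retrospective records.

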### Determination of sample size

The sample size was calculated by PASS 11.0 (NCSS Statistical and Data Analysis, USA) software and was estimated based on the preliminary research results of the Japanese clinical trial. According to previous studies with a single group design, the rate of LNM with expanded indications for ESD was 3% [20, 21] with an allowable error of 1.5%. Based on a one-sided test with an α value equal to 0.025, the estimated total sample size required for the trial is at least 497 patients. The withdrawal rate was assumed to be 20% during the follow-up. Therefore, the total sample size that is needed for this clinical study is approximately 554 patients, of which 274 and 280 are enrolled in a prospective- and retrospective study, respectively.

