### Elimination criteria

A tumor with distant metastasis that is observed during the operation and postoperatively confirmed as advanced gastric cancer (pT_2_N_0_-_3_ M_0–1_) or non-gastric cancer by pathologic examination.Patients who do not follow the research plan and receive other anti-tumor treatments during the observation period.Patients with incomplete clinical data obtained after enrollment, which cannot be used in future statistical analysis.Patients who do not comply with the research protocol for treatment.Study termination as deemed necessary by researchers for the benefit of the patient.

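### The total of about 554 does not follow from 497 patients and a 20% withdrawal rate, and whether the 1.5-point error is met depends on an unstated choice

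*Protocol article*

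**What the plan says.** All the figures are in the Protocol article, Determination of sample size. The expected rate of lymph node metastasis (LNM) is 3% and the allowable error 1.5%. The calculation is introduced as "Based on a one-sided test with an α value equal to 0.025", and the result is that "the estimated total sample size required for the trial is at least 497 patients". The next sentence reads "The withdrawal rate was assumed to be 20% during the follow-up". The paragraph then draws the consequence that "the total sample size that is needed for this clinical study is approximately 554 patients". It splits this total into 274 prospective and 280 retrospective cases.

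Three other places bear on this:

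- The total of 554 is repeated as the enrolment target in the Abstract (Methods) and in Study design and setting.
- Primary endpoint defines the outcome as the LNM rate judged by histopathology. Table 3 collects pathology at the operation.
- Elimination criteria remove patients after enrolment, among them "Patients with incomplete clinical data obtained after enrollment, which cannot be used in future statistical analysis". Neither cohort is exempted.

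**The concern.** The three numbers are presented as one chain: evaluable patients needed, expected loss, total to enrol. A reader who repeats the last step with the stated 20% does not arrive at 554. This paragraph is the only justification given for the size of the study. If its figures disagree, nobody can tell which loss rate was planned, for which patients, or how precise the primary estimate is expected to be.

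Two features make the paragraph harder to repair by guessing. The loss is described as withdrawal during follow-up, although the primary endpoint is known from the surgical specimen before follow-up starts. The calculation is also called a one-sided test, but the paragraph gives no null rate and no power.

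**Working it through.** **Inputs**, all from Determination of sample size: p = 0.03; d = 0.015; one-sided α = 0.025, so z = 1.96; evaluable N = 497; withdrawal 20%; total 554 = 274 prospective + 280 retrospective.

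**Step 1. The evaluable number.** Taking the allowable error as a confidence-interval half-width:

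n = z² p(1 − p) / d² = 1.96² x 0.03 x 0.97 / 0.015² = 496.8, rounded up to 497.

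The plan's figure reproduces. It is the half-width formula for a two-sided 95% interval. One-sided 0.025 and two-sided 0.05 share z = 1.96, so the label does not affect the number.

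**Step 2. Inflation for 20% loss over the whole sample.**

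- Standard: 497 / (1 − 0.20) = 621.25, so 622. The stated 554 is 68 lower.
- Cruder: 497 x 1.20 = 596.4, so 597. The stated 554 is 43 lower.
- Loss that 554 allows for: 1 − 497/554 = 10.3%.
- For comparison, a 10% loss gives 497 / 0.9 = 552.2, so 553.

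The word for approximation in the text cannot cover a gap of 43 or 68 patients.

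**Step 3. Can 20% be kept?** Only if it applies to about half the sample.

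- Prospective cohort only, total needed: 280 + (497 − 280)/0.8 = 280 + 271.25, so 552.
- Prospective cohort only, evaluable from the printed split: 280 + 0.8 x 274 = 499.2, about 499.
- The mirror image, retrospective cohort only: 274 + (497 − 274)/0.8 = 274 + 278.75, so 553. The arithmetic alone therefore cannot show which cohort was meant.

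The prospective-only reading leaves 499 against a requirement of 497. It tolerates the loss of about two of the 280 retrospective patients.

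**Step 4. Precision under each reading.** Half-width = 1.96 x √(0.03 x 0.97 / n):

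| Reading | Evaluable n | Half-width (points) |
|---|---|---|
| Withdrawal removes no LNM result, no other loss | 554 | 1.42 |
| 20% loss in the prospective cohort only | 499 | 1.50 |
| Plan's requirement | 497 | 1.50 |
| 20% of all patients lack a usable LNM result (0.8 x 554 = 443.2) | 443 | 1.59 |

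In the last case 443 is 54 below 497, and the half-width is 0.09 points wider than planned.

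**The case against.** The best defence is that the patients may be there and only the explanation is missing. Retrospective cases are drawn from January 2008 to April 2018 and must meet the inclusion criteria, so choosing them from existing records is a plausible reason to expect little loss. A 20% loss among prospective patients alone then gives 552, close to 554, and a condensed article might omit that allocation. This stands as a possible explanation, but it does not clear the paragraph. The rate follows directly on a total sample size and is limited to no cohort, and retrospective patients are also subject to elimination for incomplete data.

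A reader might go further and infer that the trial is short of patients and will miss its 1.5-point error. The documents do not support that. It requires 20% of all 554 patients to lack an LNM result. The 20% is worded as withdrawal during follow-up, which need not remove a result fixed at surgical pathology. The loss that can remove one is elimination, and no elimination rate is given. So 443 is one scenario, not what the design is known to deliver.

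The size is also modest. A true rate of 3.4% instead of 3% would widen the interval by the same amount at n = 497 (1.96 x √(0.034 x 0.966/497) = 1.59 points). The plan states no power or pass/fail threshold that 54 fewer patients would breach. The one-sided wording is a labelling matter and adds no weight.

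**Conclusion.** The point holds as an inconsistency in the sample size paragraph. As written, 497 and 20% give 622 (or 597), not 554, and 554 corresponds to about 10.3% loss. Either a rate near 10% was used, or 20% was applied to one cohort without saying so.

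Whether the allowable error is met cannot be settled from the document. At a 3% rate the half-width is 1.42, 1.50 or 1.59 points for 554, 499 or 443 evaluable patients. Only the last misses 1.50, by 0.09 points. These figures assume the normal approximation that produced 497 and the assumed rate of 3%.

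It should be corrected because the enrolment target rests on this paragraph and the correction is cheap. A proven loss of precision is not the reason.

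**What to change.** Rewrite the paragraph without changing enrolment:

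1. State the loss rate actually used and the cohort or cohorts it applies to.
2. Define the loss as patients not evaluable for LNM, tied to the Elimination criteria, in place of withdrawal during follow-up. The sponsor has to supply the expected rate, since the article gives none.
3. Give the evaluable number and half-width that follow. If 20% of the whole sample is meant, that is 443 and about 1.6 points. If 20% of the prospective cohort only is meant, or about 10% overall (0.9 x 554 = 498.6), it is about 499 and 1.50 points. If the prospective-only reading is used, say why almost no loss is expected among the 280 retrospective patients.
4. Describe the calculation as the half-width of a two-sided 95% confidence interval instead of a one-sided test. The 497 is unchanged.

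The cost is one paragraph of wording. Under the whole-sample reading the stated precision becomes slightly less favourable.

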### Patient and public involvement

Patients and the public were not involved in the design, the recruitment, or the conduct of the trial. The sponsor played an important role in study design, collection, management, analysis and interpretation of data, writing of the report, and the decision to submit the report for publication. They had the ultimate authority regarding any activity in the trial.

## Discussion

The optimal treatment for EGC should balance radical tumor treatment and surgical trauma reduction. However, controversy remains surrounding how to choose an appropriate treatment in patients with EGC who exceed the absolute indications for ESD. The primary endpoint of this study is the rate of LNM. The scope of potential expanded indications for ESD will be explored and evaluated based on the presence of LNM by histopathology and the positive rate of LNM with expanded indications for ESD. The purpose of this study is to explore and evaluate expanded indications for ESD that match the characteristics of the Chinese population in patients with EGC and to introduce a staging diagnosis and examination scheme for EGC that is appropriate for China. To the best of our knowledge, this study is the first clinical trial to focus on Chinese patients with EGC, and the results could facilitate clinical decision-making.

Despite decades of research on the treatment of EGC, numerous problems remain unsolved. Regarding preoperative evaluation, Choi et al. showed that the overall accuracy of endoscopic ultrasonography in T staging of gastric cancer is 78% and only 72% in T1b submucosal staging. Thus, determining the depth of tumor submucosal infiltration remains difficult, which may result in unnecessary surgical trauma to some patients [22]. Similarly, Choi et al. reported that the tumor diameter measured under the endoscope was significantly smaller than that measured pathologically. Although the size deviation in 80% of tumor lesions was < 0.4 cm, the difference suggests that preoperative gastroscopy may underestimate the tumor diameter [23]. Consequently, ESD performed in patients with expanded indications may result in non-curative resection of the tumor and, thereby, affect the prognosis of patients.

Most of the endoscopic treatments of EGC worldwide are based on the Japanese gastric cancer treatment guidelines 2018 (5th edition) [4]. Most of the existing research data on the absolute indications for ESD are from Japan and South Korea. Some studies have found that performing ESD for expanded indications can achieve a similar effect on LNM rate and patient prognosis as performing ESD for absolute indications [24, 25]. Therefore, a refinement of the expanded indications for ESD is imperative to guide clinical practice. Additionally, most of the studies on ESD or gastrectomy are retrospective in nature, and the influence of preoperative examination, surgeon, and surgical procedure may lead to bias; moreover, a detailed subgroup analysis was lacking. Further, prospective, multicenter, large-sample studies on radical gastrectomy in the Chinese population to verify the feasibility of endoscopic indications for EGC or adjust the existing endoscopic indications for EGC are limited. Hence, conducting this study to explore the expanded indications for EGC is necessary.

This study has some limitations. First, this study includes only a Chinese sample; therefore, further studies that include other populations are warranted. Second, this is a multicenter, ambispective, observational, open-cohort study; the quality of evidence may be lower than a large-sample, multicenter, randomized controlled study. Nevertheless, we will improve the research protocol further, by including more research centers and patients to provide a more precise evaluation of expanded indications for ESD and staging scheme for EGC.

